### Statistical methods

Statistical analysis, including a full analysis set based on intent-to-treat principle and a per-protocol set, will be conducted with SAS 9.4. Continuous variables described as mean ± SD or median (interquartile range) will be analyzed by *t*-test or rank-sum test while categorical variables represented by frequency (composition ratio) will be analyzed by chi-square or Fisher’s exact tests. Generalized estimating equation or mixed effect model is suitable for trends over time and treatment-time interactions. The analysis of correlation will be conducted with spearman correlation analysis. Exploratory subgroup analysis will be conducted to explore possible sources (i.e., parity status, the duration after the last childbirth, etc.) of heterogeneity and inconsistency. The confidence interval will be set at 95%, with a significance level of 5% (*p* < 0.05).

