### Randomization, allocation concealment and blinding

The random assignment scheme for this study was generated by the Clinical Research Center of LongHua Hospital Shanghai University of Traditional Chinese Medicine with “Proc plan” program of SAS 9.4 (SAS Institute, Cary, NC, United States). In this study, stratified randomization was adopted, with the research centers as the stratification factor. All the 4 participating hospitals will compete for enrollment. The random distribution cards sealed in opaque envelopes will be opened by the personnel for grouping according to the sequence of hospital visits so that patients can be assigned to sacral group, abdominal group or alternating group at 1:1:1 ratio. Based on the characteristics of this study, assessors for information and statisticians are blinded. Moreover, all researchers who have received training on the implementation of this research will strictly abide by the principle of departments separation.

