## Outcomes

The primary outcome of the study will be the change of urine leakage between baseline and week 6 measured by the 1 h pad test. The standardized procedure of the 1 h pad test requires the patients to wear a pre-weighed pad, drink 500 mL of water within 15 min, and then complete various activities including walking, going up and down stairs, standing and sitting, picking up a coin from the floor, coughing, running, and putting their hands under running water. Afterwards, the pad will be reweighed to measure the amount of urinary leakage (13). The 1 h pad test has a high adherence rate and a specificity of 65% to 89% (14). When patients have periods or a severe cough, outcome evaluations will be postponed and rescheduled until the end of the period or the remission of the cough.

The secondary outcomes include the following ten items:

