### Sample size calculation

The PASS software (version 15.0.5, NCSS, LLC) was used to calculate sample size with *α* of 0.05 (two-tailed), power of 80%, and ratio of 1:1:1. Based on our previous research, the change of urine leakage between baseline and week 6 was calculated. For the sacral, abdominal, and alternating groups, the mean ± standard deviation (SD) was 9.90 ± 2.61, 10.30 ± 3.60 and 11.60 ± 3.93, respectively (12). Assuming a 20% dropout rate, the sample size is 120 patients for each group, and 360 patients in total.

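### The only stated test that fits the primary outcome uses neither baseline leakage nor the centre strata, so it is valid but gives up precision the trial could have at no cost

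*Protocol article*

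**What the plan says.** All references are to the protocol article.

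- **Outcomes:** the primary outcome is "the change of urine leakage between baseline and week 6 measured by the 1 h pad test". Table 1 schedules urine leakage at week 0 and week 6 only.
- **Statistical methods:** continuous variables "will be analyzed by *t*-test or rank-sum test". No covariate is named and the primary outcome has no sentence of its own. The model-based methods are given another purpose: "Generalized estimating equation or mixed effect model is suitable for trends over time and treatment-time interactions".
- **Randomization, allocation concealment and blinding:** "stratified randomization was adopted, with the research centers as the stratification factor". Four hospitals enrol competitively, so centre sizes may be unequal.
- **Criteria for diagnosis** and **Criteria for inclusion:** entry is limited to mild (1.1 to 9.9 g) and moderate (10 to 49.9 g) leakage on the same 1 h pad test.
- **Sample size calculation:** the assumed mean change ± SD for sacral, abdominal and alternating "was 9.90 ± 2.61, 10.30 ± 3.60 and 11.60 ± 3.93, respectively". "Assuming a 20% dropout rate, the sample size is 120 patients for each group, and 360 patients in total".

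**The concern.** Leakage cannot fall below zero, so no patient can improve by more than her baseline value. A patient in the mild stratum has at most 9.9 g to lose, so even complete cure would not take her above the smallest planned mean change (9.90 g) or up to the other two (10.30 and 11.60 g). A patient entering at 40 g has no such limit. Change is therefore likely to vary with baseline, and a test without baseline leaves that variation in the error term. It also leaves any chance baseline difference between arms in the estimate.

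Centre raises a similar issue. Stratifying by centre balances the arms within centres. If centres differ in outcome, an analysis that ignores them does not use that balance, and its standard errors tend to be too wide.

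At stake is the precision of the contrasts between the alternating arm and the two fixed-site arms, which the Discussion presents as the purpose of the trial. The planned differences are small: 11.60 − 9.90 = 1.70 g and 11.60 − 10.30 = 1.30 g.

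**Working it through.** **1. Reproduce the stated sample size.** Inputs from Sample size calculation: means 9.90, 10.30 and 11.60; two-sided α 0.05; power 80%; 20% dropout. The grand mean is 10.60 and the sum of squared deviations is 0.70² + 0.30² + 1.00² = 1.58. Take a one-way F-test with the largest stated SD (3.93) as the common SD. At 96 per arm the noncentrality is 96 × 1.58 / 3.93² = 9.82 and power is 80.4%; at 95 per arm power is just below 80%. Then 96 / (1 − 0.20) = 120, the stated figure. So 96 evaluable per arm is the right basis below.

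**2. Power of the unadjusted two-group test** (noncentral t, 2 × 96 − 2 = 190 df, two-sided 0.05).

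- Alternating vs abdominal: SD = √((3.93² + 3.60²)/2) = 3.769. Noncentrality = 1.30 / (3.769 × √(2/96)) = 2.390. Power 66.2%.
- Alternating vs sacral: SD = √((3.93² + 2.61²)/2) = 3.336. Noncentrality = 1.70 / (3.336 × √(2/96)) = 3.531. Power 94.0%.

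**3. Add baseline as a covariate.** If change correlates r with baseline within arms, the residual SD is SD × √(1 − r²). The document does not give r, so these values are assumptions. The few degrees of freedom spent on covariates are ignored.

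| Assumed r | Variance factor 1 − r² | Residual SD (alt. vs abd.) | Power, alt. vs abd. | Power, alt. vs sacral |
|---|---|---|---|---|
| 0 | 1.00 | 3.769 | 66.2% | 94.0% |
| 0.2 | 0.96 | 3.692 | 68.0% | 94.8% |
| 0.3 | 0.91 | 3.595 | 70.3% | 95.7% |
| 0.4 | 0.84 | 3.454 | 73.7% | 96.9% |
| 0.5 | 0.75 | 3.264 | 78.4% | 98.2% |
| 0.6 | 0.64 | 3.015 | 84.4% | 99.2% |

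If the SDs at baseline and week 6 were equal, 1 − r² = (1 + ρ)/2, where ρ is the correlation between the two pad tests. Then ρ = 0.9 gives a factor of 0.95 (r about 0.22) and ρ = 0.3 gives 0.65 (r about 0.59), so the table covers that range of ρ.

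**4. Add centre alone.** If centre explains a share c of the variance of change (again an assumption), the SD is multiplied by √(1 − c). Power for alternating vs abdominal is 66.6% at c = 1% and 70.8% at c = 10%, a gain of about 0.4 to 4.6 points over 66.2%.

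**5. Can the documents support a much larger r?** Suppose improvement were proportional to a baseline spread evenly over 1.1 to 49.9 g (both assumptions). Baseline mean = 25.5 g, SD = 48.8/√12 = 14.1 g, coefficient of variation = 14.1/25.5 = 0.55. Change would have at least that coefficient of variation, so its SD would be at least 0.55 × 9.90 = 5.5, 0.55 × 10.30 = 5.7 and 0.55 × 11.60 = 6.4 g. The plan assumes 2.61, 3.60 and 3.93 g. That scenario cannot be combined with the SDs behind the power figures, so it gives no ground for an r above the tabulated range.

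**The case against.** The strongest objection is that the sentence in Statistical methods is generic. It covers all continuous variables, does not mention the primary analysis, and stands in a condensed article whose analysis plan is not shown. Covariates are often left to that plan. It is indeed an inference that the sentence governs the primary outcome. But the article names a test, and no other method in it suits a change between two time points, so the point concerns a stated choice and not silence.

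Four stronger readings are tempting, and the documents do not support them:

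- **That the unadjusted test is biased.** It is not: under randomisation the difference in mean change is unbiased, and ignoring the strata is conservative. Adjustment removes the effect of chance baseline imbalance and improves precision.
- **That the 66% shows a trial underpowered for want of adjustment.** Step 1 shows that 120 per group matches a three-group F-test; the article does not claim 80% power for each pairwise contrast. The gap between a three-group calculation and two-group tests is a separate matter that ANCOVA does not settle.
- **That leaving two tests open lets the results pick the primary test.** The article pairs mean ± SD or median (interquartile range) with the two tests, which reads as the usual choice by distribution. The criterion may well be in the analysis plan.
- **That the longitudinal models for incontinence episode frequency and ICIQ-SF lack covariates.** On these the article is merely silent, which is no finding.

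It also stands that the size of the gain cannot be determined from the documents and may be small.

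**Conclusion.** The point holds as a loss of precision, not of validity. The stated test ignores a baseline measure that is already collected and is likely to predict change, and it ignores the factor used to stratify randomisation. For alternating versus abdominal at 96 evaluable per arm, baseline adjustment would raise power from 66% to between 68% (r = 0.2) and 84% (r = 0.6). For alternating versus sacral there is little to gain, since power is already 94%. Centre adjustment alone would add about 0.4 to 4.6 points if centre explains 1% to 10% of the variance.

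These figures rest on the plan's own means, SDs and dropout rate, on assumed values of r and of the centre share, and on reading the generic sentence as covering the primary outcome. That some gain exists is well supported by the entry range and the cap on improvement; how large it is remains open. The change is worth making because it costs almost nothing.

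**What to change.** In Statistical methods, give the primary outcome its own sentence naming one analysis: an ANCOVA of week-6 pad-test leakage (or of the change) on treatment group, baseline pad-test leakage and centre, with robust standard errors. Report the adjusted group contrasts from that model with 95% confidence intervals. With baseline in the model, using week-6 leakage or change gives the same contrasts apart from sign. Robust standard errors suit the unequal SDs that the plan assumes (2.61 to 3.93 g). Keep the rank-based test as a sensitivity analysis.

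The cost is a change of wording, to be recorded as an amendment before treatment codes are released to the blinded statisticians. No patients, visits or measurements are added, because baseline leakage and centre are already recorded.

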## Methods

### Study design

This multi-center, randomized, controlled trial will be conducted at LongHua Hospital Shanghai University of Traditional Chinese Medicine, Obstetrics and Gynecology Hospital of Fudan University, Yueyang Hospital of Integrated Traditional Chinese and Western Medicine of Shanghai University of Traditional Chinese Medicine, and Seventh People’s Hospital. It has been approved by the Medical Ethics Committee of LongHua Hospital Shanghai University of Traditional Chinese Medicine (No. 2022LCSY084) and registered at ClinicalTrials Registry (NCT05635669). This protocol is reported based on Recommendations for Interventional Trials (SPIRIT) 2013 Checklist. Any amendment of the protocol will be recorded and reported. Women with SUI will be randomized into sacral group, abdominal group or alternating group at a 1:1:1 ratio. The flowchart of the trail is shown in Figure 1 while the schedule of enrollment, interventions, and assessment is presented in Table 1.

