It can be seen that the EA tolerance might be a key factor affecting the efficacy in EA treatment, but it has been rarely reported. Given that repeated stimulation of the same acupoints may lead to EA tolerance, we envisioned to provide treatments with alternating use of sacral and abdominal acupoints, which avoid the need to use the same set of acupoints every time. By adopting this approach, we aim to prevent EA tolerance caused by repeated stimulation, thus improving the clinical efficacy of the treatment.

In order to confirm the advantages of the treatment with alternating acupoints combination, a multi-center, stratified randomized study and a 48 weeks long-term follow-up with rigorous methodological design will be used to make the results more objective. In this study, the three groups will all receive acupuncture treatments (abdominal acupoints EA treatment, sacral acupoints EA treatment or alternating acupoints EA treatment), which encourage a better compliance of patients. On the other hand, we select BL33 and BL35 for the sacral group and RN3, RN4 and KI12 for the abdominal group. This is because our team’s previous investigations have demonstrated the effectiveness of EA using these acupoints in treating SUI (12, 19, 20). The positive outcomes may be attributed to EA’s capacity to address bladder neck and urethral support defects, modulate urinary bladder pressure, enhance urethral sphincter muscle tone, and reduce muscle fatigue (28–30). What’s more, the recovery of pelvic floor function is helpful for the treatment of SUI. Therefore, in addition to the use of the 1 h urinary pad test with standardized procedures, this study also used pelvic floor ultrasound for objective assessment of efficacy. At last, for medical ethical considerations, patients are allowed to receive specialty therapy for SUI during the follow-up period. The data will be collected as part of the secondary outcome, allowing us to compare the number of patients and frequency of use between the two groups. This analysis will not only offer insights into treatment effectiveness but also assess any potential sustained effects.

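### The three-arm primary outcome is assigned to two-sample tests at an unadjusted 5%, giving a false-positive chance of about 9% to 12% if any one significant pair counts as success

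*Protocol article*

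**What the plan says.** All points are from the protocol article.

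- **Design (Study design):** "Women with SUI will be randomized into sacral group, abdominal group or alternating group at a 1:1:1 ratio".
- **Primary outcome (Outcomes section):** "The primary outcome of the study will be the change of urine leakage between baseline and week 6 measured by the 1 h pad test". Table 1 schedules it at baseline and week 6 only.
- **Test (Statistical methods):** continuous variables "will be analyzed by *t*-test or rank-sum test". Generalized estimating equations or a mixed model are mentioned only for time trends and treatment-by-time interactions.
- **Error level (Statistical methods):** "The confidence interval will be set at 95%, with a significance level of 5" per cent, stated once for everything.
- **Sample size (Sample size calculation):** alpha "of 0.05 (two-tailed), power of 80%, and ratio of 1:1:1". The expected change in the sacral, abdominal and alternating groups "was 9.90 ± 2.61, 10.30 ± 3.60 and 11.60 ± 3.93, respectively". The result: "Assuming a 20% dropout rate, the sample size is 120 patients for each group, and 360 patients in total". No test is named.
- **Aim (Discussion):** "In order to confirm the advantages of the treatment with alternating acupoints combination".

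**The concern.** A t-test compares two groups. It can be applied to three arms only as separate pairs, and the single 5% level then applies to each pair unless something else is said. The aim is confirmatory. A claim for alternating could rest on one nominal p < 0.05 out of two or three chances, with a real error rate above the 5% that the article states.

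The sample size points to a different test from the analysis section. An analysis plan that follows the article's wording inherits the problem, and one that departs from it contradicts the article. Either way the analysis wording needs correcting, so this is more than detail left to an analysis plan.

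**Working it through.** **Inputs.** Means 9.90, 10.30, 11.60 and SDs 2.61, 3.60, 3.93 (sacral, abdominal, alternating); two-sided alpha 0.05; power 80%; dropout 20%; 120 per group. Evaluable per group: 120 × 0.80 = 96.

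**1. The plan's own figure.**

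Overall one-way F test:
- Grand mean: (9.90 + 10.30 + 11.60)/3 = 10.60.
- Squared deviations: 0.70² + 0.30² + 1.00² = 0.49 + 0.09 + 1.00 = 1.58.
- Noncentrality with 96 per group and common SD 3.93: 96 × 1.58 / 3.93² = 151.68 / 15.44 = 9.82.
- With 2 and 3 × 96 − 3 = 285 degrees of freedom, power is 80.4%. Then 96/0.80 = 120, the stated number.
- This depends on the SD. The root-mean-square SD of 3.43 gives 73, then 92 after dropout. An SD of 3.60 gives 81, then 102.

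Two-sample comparisons at 0.05, n = (1.96 + 0.84)² × (SD₁² + SD₂²) / difference², with (1.96 + 0.84)² ≈ 7.849 before rounding:
- Alternating vs sacral: 7.849 × (15.44 + 6.81)/1.70² → 61, then 77.
- Alternating vs abdominal: 7.849 × (15.44 + 12.96)/1.30² → 132, then 165.
- Sacral vs abdominal: 7.849 × (6.81 + 12.96)/0.40² → 970, then 1213.

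None of the pairwise tests at the stated alpha gives 120.

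**2. Familywise error when all groups are equal.**
- *Three pairs at 5%.* At least one rejection means that the range of three standardised means exceeds 1.96 × √2 = 2.77. The studentized-range probability is 12.2%. Simulation with the listed SDs gives 12.1%. For comparison, assuming independence gives 1 − 0.95³ = 14.3%, and the upper bound is 3 × 5% = 15%.
- *Two alternating contrasts at 5%.* Either rejects: 5% + 5% − P(both) = 10% − 0.93% = 9.1%. With the listed SDs it is about 8.7%.
- *Alternating must beat both.* Both contrasts reject with probability 0.93% when all three groups are equal. When alternating equals only one of the others, the chance is at most the 5% of that single test. There is no inflation.

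**3. Power with 96 evaluable per group, listed means and SDs, unadjusted.**
- Alternating vs sacral: SE = √(22.26/96) = 0.4815; 1.70/0.4815 − 1.96 = 1.57 → 94%.
- Alternating vs abdominal: SE = √(28.40/96) = 0.5440; 1.30/0.5440 − 1.96 = 0.43 → 67% (66% in simulated trials).

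**4. Effect of the remedies (simulated trials, 96 per group).**

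| Procedure | Alternating vs sacral | Alternating vs abdominal |
|---|---|---|
| Unadjusted pairs | 94% | 66% |
| F test first, then pairs at 5% | 89% | 66% |
| Hochberg on the two alternating contrasts | 91% | 66% |

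Familywise error with the F test first is 4.9% under equal SDs and 5.2% under the listed unequal SDs.

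**The case against.** The strongest reply has four parts.

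- **Generic wording.** The sentence on t-tests covers all continuous variables. It does not mention the primary outcome, list contrasts or say that each pair is judged at 5%. Contrasts and adjustment are often left to an analysis plan, which is not shown. "Rank-sum" might loosely mean a Kruskal–Wallis test, and a treatment-by-time term could in principle compare three groups. This stands in part: 5% per pair is an inference from one unadjusted level. But the primary outcome is continuous, the t-test is a two-sample test, and the article does not link the longitudinal model to the primary outcome. The named test does not fit the design.
- **The 12% figure.** A reader might infer that the plan's error rate is 12%. The article does not support that: it requires all three pairs to be tested and any one to count. A false sacral-versus-abdominal difference says nothing for alternating, so about 9% fits the stated aim better. Counting only false claims that alternating is better than at least one comparator, the figure is about 4.5%, against 2.5% in that direction for a single two-sided test. This stands, and the size is given as a conditional range.
- **The sample size.** A reader might also infer that 120 proves an ANOVA was planned. It does not: the match needs the largest SD as common to all arms. Some reduced-alpha variants land close by (F test at 0.0167 with SD 3.43 gives 119; F test at 0.025 with SD 3.60 gives 120; a t-test of the 1.70 difference at 0.0167 with SD 3.60 gives 120). None of these uses the stated 0.05.
- **Loose wording rather than a flawed plan.** If an overall F test was intended, the analysis section may simply be badly phrased. That is possible, and the correction is the same.

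**Conclusion.** The point holds in conditional form. The article names two-sample tests at an unadjusted 5% for a three-arm primary outcome with a confirmatory aim. If any one significant pair counts as success, the chance of at least one false positive is about 9% for the two alternating contrasts and about 12% for all three pairs. If alternating must beat both groups there is no inflation, but no such rule is stated.

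The analysis wording also does not match the most direct reconstruction of the sample size, an overall F test at 0.05 with common SD 3.93. That match is an inference, because the article names no test there.

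**What to change.** Amend the Statistical methods section in one of two ways, before the group results are seen:

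1. Make a three-group ANOVA of the change in urine leakage at week 6 the primary test, at two-sided 5%. Only if it is significant, test the three pairs, each at 5%. With exactly three groups this is a closed procedure and keeps the familywise error at about 5%.
2. Or name alternating vs sacral and alternating vs abdominal as the two primary contrasts and control them by Hochberg or Holm.

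In either case, state which result supports the claim for alternating, and name the test and SD behind the 120 per group in the Sample size calculation so that the two sections agree.

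The cost is about a paragraph of text, with no extra patients. Alternating vs sacral loses about 3 to 5 points of power (94% to 89–91%); alternating vs abdominal loses almost none, though it stays near 66% under the article's own assumptions. Plain Bonferroni at 0.025 for two contrasts is a poorer choice: power for alternating vs abdominal falls to 56%, and restoring 80% would need 160/0.80 = 200 per group.

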### Quality control, data management and monitoring

Prior to the study, researchers will receive training on the protocol, the standard operating procedures, and the scale evaluation in order to increase the validity of clinical research. The acupuncture therapist for this study must be a licensed acupuncturist with at least 5 years’ clinical experience. Prior to the trial, the acupuncturist will receive rigorous standardized training on acupuncture point positioning, acupuncture technique specifications, and how to use the EA equipment. Moreover, a detailed data management plan has been set, including the collection, entry, and management of data. Data collected by CRF will be entered and confirmed independently by two researchers in order to guarantee the consistency. In addition, study progress and data quality checks will be made by research assistants and monitors.

